## Abstract

**Background:**

Death with a functioning allograft has become the leading category of graft loss in kidney transplant recipients at all time points. Previous analyses have demonstrated that causes of death in kidney transplant recipients are predominated by comorbidities strongly associated with immunosuppressant medications. Adverse drug events (ADEs) have been strongly associated with nonadherence, health care utilization, and graft loss; clinicians face a difficult decision on whether making immunosuppressant adjustments in the face of ADEs will improve symptomology or simply increase the risk of acute rejection. Clinicians also face a treatment quandary in 50% of kidney transplant recipients with stage 3 or worse chronic kidney disease at 1 year post transplantation, as progressive decline in renal function has been strongly associated with inferior allograft survival.

**Objective:**

The primary objective of the CLinical Utility of the omnigrAf biomarkeR Panel In The Care of kidneY Transplant Recipients (CLARITY) trial is to evaluate change in renal function over time in kidney transplant recipients who are undergoing OmniGraf monitoring in conjunction with monitoring of their medication-related symptom burden (MRSB). A secondary objective of this study is to identify the impact of OmniGraf use in conjunction with patient-reported MRSB as part of clinical care on patients’ self-efficacy and quality of life.

**Methods:**

CLARITY is a 3-year prospective, multisite, observational study of 2000 participants with a matched control, measuring the impact of real-time patients’ MRSB and the OmniGraf biomarker panel on change in renal function over time. Secondary outcome measures include the Patient-Reported Outcomes Measurement Information System (PROMIS) Self-Efficacy for Managing Chronic Conditions–Managing Medications and Treatment–Short Form 4a; the PROMIS-29 Profile (version 2.1); the PROMIS Depression Scale, hospitalizations—subcategorized for hospitalizations owing to infections; treated rejections, MRSB, and proportion of participants with overall graft survival at year 3 post transplantation; graft loss or death during the 3-year study follow-up period; and change in provider satisfaction.

**Results:**

The primary outcome measure of the study will be a comparison of the slope change in estimated glomerular filtration rate from baseline to the end of follow-up between study participants and a matched control group. Secondary outcome measures include changes over time in PROMIS Self-Efficacy for Managing Chronic Conditions–Managing Medications and Treatment–Short Form 4a, the PROMIS-29 Profile (version 2.1), and PROMIS Depression Scale in the study group, as well as a comparison of hospitalizations and causes, rejections, and graft and patient survival compared between participants and a matched cohort. The anticipated first enrollment in the study is October 2022 with data analysis and publication expected in October 2027.

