Clinicians also find themselves in a clinical quandary when faced with patients with poor graft function. According to the most recent Organ Procurement and Transplantation Network and Scientific Registry of Transplant Recipients Annual Data Review [5], 50% of kidney transplant recipients have stage 3 chronic kidney disease (CKD) or worse at 1 year post transplantation. A large international analysis by the Patient Outcomes in Renal Transplantation investigators demonstrated that patients with stage 3b CKD or lower at 1 year post transplantation were at a significantly higher risk of graft failure by 10 years post transplantation—a risk that increased with a decrease in the estimated glomerular filtration rate (eGFR) [10]. Clinicians are aware of this, but they must also consider the risk of acute rejection that increases whenever immunosuppression is altered.

The OmniGraf biomarker panel (Transplant Genomics, Inc) includes the TruGraf peripheral blood expression profile and the Viracor TRAC donor-derived cell-free DNA test, which have demonstrated a strong ability to identify immune quiescence in stable patients post kidney transplantation, with a negative predictive value of 94% when both tests are negative and a positive predictive value of 89% for subclinical rejection when both tests are positive [11,12].

Because of the strong “rule out” capabilities of OmniGraf, it would be an ideal complement to real-time ADE knowledge and eGFR awareness to help guide clinicians’ decisions to adjust (or not) the immunosuppressive regimen and help provide a dialogue between patients and clinicians on the risk-benefit of medication adjustments. With its ability to both “rule out” and “rule in” subclinical rejection, it would also be an ideal tool to help monitor patients during and after medication adjustments. Allowing patients to express their ADEs and the impact they have on their lives, along with frank discussions with clinicians and risk-benefit of medication adjustments, may help increase patient engagement and activation. This is a key goal to help minimize the burden of symptoms and increase life participation [13].

Therefore, the aim of this study is to evaluate change in renal function over time in kidney transplant recipients who are undergoing OmniGraf monitoring in conjunction with patients’ medication-related symptom burden (MRSB) monitoring.

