### Eligibility

#### Inclusion Criteria

Participants must be adult (≥18 years of age) recipients of a primary or subsequent kidney transplant, between 3 months and 2 years post transplantation, selected by their provider to undergo OmniGraf testing as part of posttransplantation care, and provide written informed consent and Health Insurance Portability and Accountability Act authorization.

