**11A. How troublesome is it?**
Not at allVery littleModerately troublingVery troublingExtremely troubling

**Table 1 table1:** Schedule of assessments.

Enrollment or months post enrollment			Baseline visit (days –90 to 0)		3		6		9		12		15		18		21		24		27		30		33		36		Unscheduled visit		At workup for referral to transplant center
Visits	Details																														
Informed consent	Prior to any study-related procedures	✓																													
Assessment inclusion or exclusion criteria			✓																												
Participant’s demographics	Date of birth, sex, race, height, weight, and date of transplant	✓																													
Transplant information	Donor type and cause for renal failure	✓																													
Chemistry panel	Serum creatinine	✓		SOC^a^		SOC		SOC		SOC		SOC		SOC		SOC		SOC		SOC		SOC		SOC		SOC		SOC		SOC	
Immunosuppression medications	Name and changes in dose or medication			✓		✓		✓		✓		✓		✓		✓		✓		✓		✓		✓		✓		✓		✓	
Assessment of clinical events	Rejections, infections, graft Loss, and death	✓		✓		✓		✓		✓		✓		✓		✓		✓		✓		✓		✓		✓		✓		✓	
OmniGraf results	TruGraf and TRAC test results (if SOC laboratory tests are performed)	✓ (day 0)		✓		✓		✓		✓		✓		✓		✓		✓		✓		✓		✓		✓		✓		✓	
Patient’s medication-related symptom burden			✓		✓		✓		✓		✓		✓		✓		✓		✓		✓		✓		✓		✓		✓		✓
Biopsy information	Surveillance and for-cause: in case of rejection, type and grade			SOC		SOC		SOC		SOC		SOC		SOC		SOC		SOC		SOC		SOC		SOC		SOC		SOC		SOC	
Patient-reported outcomes	PROMIS^b^-29, PROMIS Self-Efficacy, and PROMIS Depression Scale	✓								✓								✓								✓					
Provider satisfaction			✓								✓								✓								✓				

^a^SOC: standard of care.

^b^PROMIS: Patient-Reported Outcomes Measurement Information System.

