Physicians can use the MRSB and OmniGraf results as they see fit, along with other clinical laboratory tests and information; however, they will be provided with a potential framework for integrating the information into their practice (Figure 1). In short, clinicians will see participants and review the MRSB portal and clinical laboratory tests, including OmniGraf. If the clinician notes that the participant has less than ideal renal function or has an MRSB that is troubling him/her, a discussion can be had between the clinician and participant. A clinical workup for the renal function or ADE can be performed to identify other treatable causes. If it is determined that the ADE (including renal function) is caused by or exacerbated by medications that the participant is taking, the laboratory findings and OmniGraf biomarker results can be used within the clinician-participant discussion to help determine the risks and benefits of adjusting medications to mitigate the ADE. OmniGraf results can also provide additional information to clinicians regarding participants who do not have a low eGFR or ADE, assisting in their clinical decision-making or identifying participants who may be at risk of subclinical inflammation.

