## Results

### Results Overview

The primary outcome measure of this study will be the slope change in renal function over time in kidney transplant recipients who are undergoing OmniGraf monitoring in conjunction with MRSB monitoring. Secondary outcome measures include the PROMIS Self-Efficacy for Managing Chronic Conditions–Managing Medications and Treatment–Short Form 4a; the PROMIS-29 Profile (version 2.1); the PROMIS Depression Scale, hospitalizations—subcategorized for hospitalizations owing to infections; treated rejections, MRSB, and the proportion of participants with overall graft survival at year 3 post transplantation; graft loss or death during the 3-year study follow-up period; and change in provider satisfaction.

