### Study Endpoint Definitions and Assessment Plan

The following will be used to define and assess events within this study.

The primary endpoint is a comparison of the slope change in eGFR from baseline to the end of follow-up between the study participants and a matched control group. eGFR will be calculated using the 4-variable Modification of Diet in Renal Disease equation [16], with a sensitivity analysis performed using the Chronic Kidney Disease Epidemiology Collaboration equation [17]. Routine serum creatinine concentrations, which are measured as a part of usual care, will be utilized to estimate the GFR at baseline and at months 12, 24, and 36 post enrollment for assessments. The slope in eGFR change will be calculated for the entire follow-up for the primary outcome, with subanalyses performed between the other described time points. The matched control group will be a propensity-matched cohort from the US Medicare database.

Furthermore, we will compare the PROMIS Self-Efficacy for Managing Chronic Conditions–Managing Medications and Treatment–Short Form 4a scores at the end of follow-up relative to baseline [18]. This will measure changes in self-efficacy within the participant population—the belief that one can carry out a behavior necessary to reach a desired goal, even when a situation contained unpredictable and stressful elements. The study coordinator will provide access to the survey at baseline and at months 12, 24, and 36 post enrollment. Subanalyses will be performed among all time points.

We will then compare the PROMIS-29 Profile (version 2.1) scores at the end of follow-up relative to baseline [19]. This will measure changes in overall quality of life and satisfaction. The study coordinator will provide access to the survey at baseline and at months 12, 24, and 36 post enrollment. Subanalyses will be performed among all time points.

This will be followed by a comparison of the PROMIS Depression Scale scores at the end of follow-up relative to baseline [20]. This will measure changes in symptoms of depression. The study coordinator will provide access to the survey at baseline and at months 12, 24, and 36 post enrollment. Subanalyses will be performed among all time points.

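### The between-group comparison of rejections is open to detection bias: participants have a panel meant to reveal subclinical rejection, and nothing in the matching or the endpoint equalizes detection in the Medicare cohort

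*Protocol article*

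**What the plan says.** The abstract's Results paragraph promises "as well as a comparison of hospitalizations and causes, rejections, and graft and patient survival compared between participants and a matched cohort". The abstract's Methods paragraph and the Results Overview name a narrower outcome; the latter lists "treated rejections, MRSB, and the proportion of participants with overall graft survival at year 3 post transplantation". The section Study Endpoint Definitions and Assessment Plan gives the source of controls: "The matched control group will be a propensity-matched cohort from the US Medicare database".

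Participants must be "selected by their provider to undergo OmniGraf testing as part of posttransplantation care" (Inclusion Criteria). Table 1 places OmniGraf at day 0, every 3 months to month 36 and at unscheduled visits, provided that standard-of-care laboratory tests are done. The Introduction credits the panel with "a positive predictive value of 89% for subclinical rejection when both tests are positive". Resources and Biomarker Testing adds that, in participants with neither low eGFR nor an adverse drug event, results can help by "identifying participants who may be at risk of subclinical inflammation".

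Biopsies in participants are standard of care and not mandated. Table 1 describes the biopsy item as "Surveillance and for-cause: in case of rejection, type and grade". The matching variables under Primary Analysis are sex, race, time from transplant, donor type and baseline eGFR.

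**The concern.** A count of treated rejections depends on how many rejections occur and on how many are found. The panel under study acts on the second. Rejection without symptoms or a creatinine rise is what it is meant to uncover. If such a case is biopsied and treated, it enters the participants' count. The same case in a control enters only if something else uncovers it. None of the matching variables reflects surveillance biopsy, biomarker use or testing intensity.

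The Introduction names acute rejection as the risk that clinicians weigh when they alter immunosuppression, so readers will look to this comparison for reassurance or warning. An undivided count cannot separate rejection that follows medication changes from rejection found by the panel. An excess could be detection alone, and equality could hide a real change in clinical rejection.

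**Working it through.** **No figure to reproduce.** The article gives no rejection rate, effect size, margin or power for rejection. What follows is an illustration, not an estimate for this trial.

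**Inputs from the article.** Positive predictive value 0.89 when both tests are positive (Introduction). Enrolment 2000, with 50% dropout and a further 50% loss or missing data (Sample Size Requirements), which leaves 2000 × 0.5 × 0.5 = 500.

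**Assumed inputs.**
- True rejection is equal in the two groups.
- Control 3-year treated rejection is 8% (range 5% to 12%).
- 5% of participants are ever positive on both tests, and half of these are biopsied.
- Every confirmed case is treated, and none would later have presented clinically.
- Matching is 1:1 (the article states no ratio), and the two groups are treated as independent samples.

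**Extra cases found.** P(both positive) × P(biopsied) × predictive value = 0.05 × 0.50 × 0.89 = 0.022, or 2.2 points.

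**Observed comparison.** 8.0% + 2.2% = 10.2% v 8.0%. Ratio 0.10225/0.080 = 1.28, with no true difference.

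**Chance of a nominally significant excess** (two-sided 5% test of two proportions, normal approximation):
- At 2000 per group, SE = √[(0.10225 × 0.89775 + 0.08 × 0.92)/2000] = 0.0091. Then 0.02225/0.0091 = 2.45, and Φ(2.45 − 1.96) ≈ 0.69.
- At 500 per group, SE = 0.0182. Then 0.02225/0.0182 = 1.22, and Φ(1.22 − 1.96) ≈ 0.23.
- At 2000 per group, over the control range, the chance is about 84% at 5% and about 55% at 12%.

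**A heavier scenario.** If 10% are both-positive and 75% of these are biopsied, 0.10 × 0.75 × 0.89 = 6.7 points are added. The ratio at 8% is 0.14675/0.080 = 1.83, and a significant excess is almost certain at 2000 per group.

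**If controls are searched too.** A second set of assumptions takes clinical rejection at 5% to 10% and subclinical rejection at 5% to 20%, the same in both groups. Observed risk = clinical + subclinical × share found and treated.

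| Share found: participants v controls | Apparent ratio | Chance of false excess, 500 per group | 2000 per group |
|---|---|---|---|
| 25–50% v 0% | 1.12 to 3.0 | 9% to nearly 100% | 25% to nearly 100% |
| 50% v 25% | 1.11 to 1.5 | 9% to 67% | 23% to nearly 100% |
| 50% v 50% | 1.0 | 2.5% | 2.5% |

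The bias comes from unequal detection. It does not need controls to be wholly unsearched, and it disappears only when detection is equal. A larger sample does not shrink the ratio; it makes a false excess more likely to be called significant.

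**The case against.** Several stronger readings are tempting, and the article does not support them.

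- *Controls are never searched for subclinical rejection.* The article does not say what surveillance biopsy or biomarker testing the Medicare cohort receives. Table 1 treats surveillance biopsy as standard of care, so some control surveillance is plausible.
- *A positive panel leads to biopsy and treatment.* Physicians may use results at their discretion, the framework is only suggested, and its figure is not shown. Testing itself follows standard-of-care laboratory work.
- *The bias must inflate rejection in participants.* The article stresses the panel's rule-out strength. A negative result could avert a biopsy and lower the number of rejections found.
- *This is the key safety comparison.* Rejection is one of several secondary outcomes. Hospitalizations, graft failure and death, which depend less on biopsy, are also compared.

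It is also fair to say that restricting the outcome to treated rejections narrows the bias, that the illustration rests almost wholly on assumed rates, and that an article leaves detailed definitions to the full protocol or analysis plan.

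These points limit the size and certainty of the claim but do not remove it. The article commits to a comparison in which the test under study can alter how often the outcome is found in one group. That is more than absent detail, and what prompted a biopsy is best recorded as it happens. Uncertainty about direction is itself a reason not to read the difference as an effect on rejection.

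**Conclusion.** The concern holds in a limited form. As planned, the rejection comparison can show a difference produced by testing alone. An apparent excess in participants is the likelier direction, but the opposite is possible. The size cannot be derived from the article. On the stated assumptions the ratio is 1.28, with about a 69% chance of nominal significance at 2000 per group and about 23% at 500. The 500 is the number left evaluable for the primary outcome, used here as a cautious lower figure; people lost before the end of follow-up may still contribute rejection events. The point concerns a secondary outcome and leaves the eGFR slope analysis untouched. It should be corrected before any conclusion is drawn from the rejection comparison.

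**What to change.** 1. Use treated rejections as the outcome wherever it is named (abstract Methods, abstract Results and Results Overview), and identify it by the same stated rule in participants and in the Medicare data.
2. Record prospectively whether each biopsy or treated rejection was prompted by an OmniGraf result, by surveillance or by clinical presentation. Report the three categories separately in participants.
3. Compare clinically presenting rejection with the cohort only if Medicare data can be classified the same way. If they cannot, removing subclinical cases from participants alone would bias the comparison in the intervention's favour.
4. Otherwise label the between-group comparison descriptive, show it with and without OmniGraf-prompted cases as bounds, and draw no safety or efficacy conclusion from it. The bounds address added detection only; they do not capture biopsies averted by a negative panel.

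**Cost.** One extra form field, changes to the endpoint wording, and work to establish what the Medicare data can distinguish. The clinical-rejection comparison would have fewer events and less precision, and the permitted conclusion is weaker. No extra visits or biopsies are needed.

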**Conclusions:**

Through this report, we describe the study design, methods, and outcome measures that will be utilized in the ongoing CLARITY trial.

**Trial Registration:**

ClinicalTrials.gov NCT05482100; https://clinicaltrials.gov/ct2/show/NCT05482100

**International Registered Report Identifier (IRRID):**

PRR1-10.2196/41020

## Introduction

The survival benefits of kidney transplantation in the United States are well documented [1,2]. Improvements in immunosuppression, better antimicrobial agents, and other aspects of ancillary care have resulted in significant improvements in short-term outcomes; however, there has been little improvement in long-term graft loss [3,4]. While the most recent Organ Procurement and Transplantation Network and Scientific Registry of Transplant Recipients Annual Data Review [5] shows that death-censored allograft failure has been improving at all time points, death with a functioning allograft has remained stable and is now responsible for more than half of graft losses at each time point. A multicenter analysis of specific causes of kidney allograft loss demonstrated that causes of death were predominated by comorbidities with strong associations with immunosuppressive medications, including cardiovascular and infectious diseases and cancers [6]. Further, a more recent analysis [7] found that 65% of kidney transplant recipients seeking hospital readmission had adverse drug events (ADEs) that were considered contributory, and ADE-associated readmissions had a significantly higher hazard of graft loss and death than readmissions without an ADE. ADEs have also been identified as a predictive factor for medication adherence in a large multicenter study. Couzi et al [8] also found that physicians significantly underestimated the prevalence of adverse events when compared to patient self-reporting. While assessments of the impact of real-time knowledge of adverse events on mutability of readmissions and outcomes are lacking, a randomized controlled trial [9] of a mobile health intervention that included real-time ADE tracking demonstrated significant reductions in hospitalizations and grade 3 or higher ADEs. Even with knowledge of ADEs, clinicians may be reluctant to adjust immunosuppressive medications owing to concerns of rejection risk during the period of medication adjustment.

Clinicians also find themselves in a clinical quandary when faced with patients with poor graft function. According to the most recent Organ Procurement and Transplantation Network and Scientific Registry of Transplant Recipients Annual Data Review [5], 50% of kidney transplant recipients have stage 3 chronic kidney disease (CKD) or worse at 1 year post transplantation. A large international analysis by the Patient Outcomes in Renal Transplantation investigators demonstrated that patients with stage 3b CKD or lower at 1 year post transplantation were at a significantly higher risk of graft failure by 10 years post transplantation—a risk that increased with a decrease in the estimated glomerular filtration rate (eGFR) [10]. Clinicians are aware of this, but they must also consider the risk of acute rejection that increases whenever immunosuppression is altered.

The OmniGraf biomarker panel (Transplant Genomics, Inc) includes the TruGraf peripheral blood expression profile and the Viracor TRAC donor-derived cell-free DNA test, which have demonstrated a strong ability to identify immune quiescence in stable patients post kidney transplantation, with a negative predictive value of 94% when both tests are negative and a positive predictive value of 89% for subclinical rejection when both tests are positive [11,12].

Because of the strong “rule out” capabilities of OmniGraf, it would be an ideal complement to real-time ADE knowledge and eGFR awareness to help guide clinicians’ decisions to adjust (or not) the immunosuppressive regimen and help provide a dialogue between patients and clinicians on the risk-benefit of medication adjustments. With its ability to both “rule out” and “rule in” subclinical rejection, it would also be an ideal tool to help monitor patients during and after medication adjustments. Allowing patients to express their ADEs and the impact they have on their lives, along with frank discussions with clinicians and risk-benefit of medication adjustments, may help increase patient engagement and activation. This is a key goal to help minimize the burden of symptoms and increase life participation [13].

Therefore, the aim of this study is to evaluate change in renal function over time in kidney transplant recipients who are undergoing OmniGraf monitoring in conjunction with patients’ medication-related symptom burden (MRSB) monitoring.

